### Power analysis

Power for the hypothesized intervention effects was estimated using Monte Carlo studies. For longitudinal mixed models, a simulation was conducted (per example by Gelman and Hill) [89] using the *R* software, and power for mediation models was estimated using simulations in the *Mplus* software [90]. Culturally adapted interventions for other mental health problems have produced effect sizes of .45 [91]. The proposed effect size is informed by our previous study, which produced effect sizes between .25 and .32 with an average effect size of .28 [20, 92]. For this study, we estimated effect sizes equivalent to *d* = .28 for continuous outcomes and *h* = .28 for binary outcomes (nearly a 50 % increase in treatment utilization), using effect sizes for mixed models that are equivalent to these classical effect sizes [93].

Power estimates were derived as the proportion of significant effects (two-tailed α = .05) across like simulations [94]. We simulated 10,000 data sets of 400 observations under the assumption that missing data will be ameliorated with the strategies described in the missing data section, and all participants will contribute data to the analysis. Intraclass correlation was simulated at .65 based on the intraclass correlations observed in our prior study. Power was .81 for continuous outcomes, and .83 for binary outcomes. A power analysis for a moderation effect by simulating a three-way interaction between treatment, time, and a moderator (e.g., familism) was conducted. Per Kraemer and colleagues’ recommendations, the interaction was examined using plots, confidence intervals, and *p* values [95]. We investigated the power for a hypothesized contrast at high, and low levels of a moderator (e.g., low v. high acculturative stress in participants in CA-BMI) through a simple slope contrast at 1 SD ± the moderator mean for participants [96]. Power for an effect size equivalent to *d* = .29 was .78 for a continuous outcome, and power for an effect size equivalent to *h* = .27 was .82 for a binary outcome. Power analysis for the proposed mediation model was conducted using a Monte Carlo simulation [90]. Using standardized regression coefficients, we conducted a simulation for 10,000 data sets in which the path from the intervention to the mediator was .12 (equivalent to *d* = .22), and the path from the mediator to the outcome was .30 for standardized variables, reflecting the stronger relation that we anticipate between the mediators and outcomes. The Monte Carlo simulation indicated that power for the indirect effect was .77. Thus, accounting for a potential 20 % participant attrition, the proposed sample size should provide sufficient power for all planned analyses.

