### Design and procedure

In this comparative effectiveness study, we will recruit 600 English- or Spanish-speaking heavy-drinking men of Mexican origin who are admitted to the hospital for medical treatment of an alcohol-related injury or heavy drinking. Participants will be randomized to receive a CA-BMI or NA-BMI. The primary outcomes of interest are alcohol use, alcohol problems, help-seeking, and treatment utilization. Follow-up assessments will be completed at 3, 6, and 12 months post-treatment. See Fig. 1.

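### The mediation power of .77 is attached to two effect sizes that disagree: a standardized path of .12 is d of about .24, not d = .22

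*Protocol article*

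**What the plan says.** The Power analysis section of the protocol article describes the mediation simulation in a few sentences. The scale of the inputs is given by "Using standardized regression coefficients, we conducted a simulation for 10,000 data sets". The first input is that "the path from the intervention to the mediator was .12 (equivalent to *d* = .22", and the second is that "the path from the mediator to the outcome was .30 for standardized variables". The result follows: "The Monte Carlo simulation indicated that power for the indirect effect was .77". The section then concludes: "Thus, accounting for a potential 20 % participant attrition, the proposed sample size should provide sufficient power for all planned analyses".

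The same section sets the test level for its power estimates: "Power estimates were derived as the proportion of significant effects (two-tailed α = .05". The only simulated sample size it prints is in "We simulated 10,000 data sets of 400 observations", and that belongs to the mixed-model simulation. No sample size is printed for the mediation simulation. Under Design and procedure the article says that "we will recruit 600 English- or Spanish-speaking heavy-drinking men of Mexican origin", and the Abstract gives about 300 per condition.

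**The concern.** The path and its d are offered as one quantity on two scales, so one should convert into the other. With two arms of equal size they do not. One printed input to the .77 is therefore wrong, and a reader cannot tell which effect the .77 refers to.

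Mediation is the planned test of how the adapted intervention is meant to work: through temptation and confidence, and through support from family and friends (section on the culturally adapted intervention; Approach to analyses). The stated .77 is already the lowest power in the section, and the closing sentence covers it with a general statement of sufficiency. How much weight a null indirect effect can bear depends on which effect the .77 belongs to.

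**Working it through.** **Inputs.** Path a = .12 (standardized), stated d = .22, path b = .30, two-sided alpha .05, power .77 and 20% attrition come from Power analysis. N = 600 comes from Design and procedure, and about 300 per arm from the Abstract. After attrition, 600 × .80 = 480. The N of the mediation simulation is not stated, so 400, 480 and 600 were tried.

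**Conversion.** An equal two-arm indicator has SD √(.5 × .5) = .5.
- Path to d: .12/.5 = .24, or by the point-biserial formula d = 2r/√(1 − r²) = .24/√.9856 = .242.
- d to path: r = d/√(d² + 4) = .22/√4.0484 = .109.
- Rounding: paths of .115 to .125 give d = .23 to .25. Values of d from .215 to .225 give paths of .107 to .112. The ranges do not meet.
- Unequal allocation widens the gap (d = .247 at 40:60). If only the mediator were standardized, .12 would be d = .12, further still from .22.

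**Which path limits the test.** For b at N = 480 the noncentrality is .30 × √(480 × .9856)/√.91 = 6.84, so its power is essentially 1. The power of the indirect effect is governed by a.

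**Reproducing .77.** In a simple observed-variable model without covariates, power for a is Φ(a√N/√(1 − a²) − 1.96). The joint-significance test multiplies this by the power for b. Results, with a 10,000-data-set simulation in brackets:

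| N | path .12 | d = .22 (path .109) |
|---|---|---|
| 400 | .676 (.680) | .595 (.600) |
| 480 | .754 (.757) | .674 (.675) |
| 500 | .771 (.770) | .691 (.693) |
| 600 | .842 (.843) | .769 (.767) |

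Two combinations come close to the printed .77: path .12 with about 480 to 500 analysed, or d = .22 with all 600. Solving for exactly .77 gives N of about 499 and 602. The article does not name the test of the indirect effect. A Sobel test is less powerful: by formula, path .12 reaches .77 at N of about 573 and d = .22 at about 676.

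**If .12 was simulated.** Power of .77 implies a noncentrality of .739 + 1.96 = 2.699. Scaled to d = .22, 2.699 × .1093/.12 = 2.458, so power is Φ(2.458 − 1.96) = .69. Working through the back-solved N gives .690 (joint) or .700 (Sobel). Holding .77 for d = .22 would take (.12/.1093)² = 1.205 times the sample, about 20% more.

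**If d = .22 was simulated.** In the simple model .77 is reached only with all 600 analysed. At 480 it is .674, about .67.

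**The case against.** The mismatch is .02 SD inside a parenthesis. On the literal reading, .77 is the correct power for the path that was run and only its translation is wrong. The article does not set d = .22 as a target for the mediator. Correcting the label to d = .24 changes no power figure, and .24 is still below the .28 assumed for the outcomes. This stands, and it is one of the two acceptable repairs.

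A reader might infer something stronger: that the true mediation power is .69 and the article overstates it by 8 points. The documents do not support that. They do not say whether .12 or d = .22 was the simulation's input, nor at what N. If d = .22 was the input with 600 analysed, .77 is already its power.

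Nor is a shortfall after attrition shown. Approach to analyses plans latent growth models in which the mediator's growth factor is regressed on baseline mediator and outcome; the table above uses observed variables and no covariates. Suppose, as an assumption not in the documents, that baseline covariates explain 20% of the mediator's variance. Then path .12 at 400 gives Φ(.12√400/√(1 − .0144 − .20) − 1.96) = .773, and d = .22 at 480 gives .770. On that account the 480 men left after attrition would hold .77 for d = .22.

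A latent path of .12 could also match an observed-scale d of .22 if reliability were about (.22/.242)² = .83. The article states no such conversion; it reports standardized coefficients and calls the two figures equivalent. That leaves open an explanation which the authors could supply, but it does not reconcile the printed figures.

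**Conclusion.** The two printed figures disagree, and rounding or unequal allocation does not reconcile them. With equal arms and an observed mediator, .12 is d of about .24 (.23 to .25) and d = .22 is a path of about .11. The .77 can belong to only one of them.

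The consequence is conditional. If .12 was simulated, .77 is the power for d of about .24, and power for d = .22 at the same N is about .69 to .70. If d = .22 was simulated, .12 is wrong; in the simple model with the joint-significance test, .77 then needs all 600 analysed, and power is about .67 at 480. These absolute values assume equal arms, no covariate gain and no measurement error. They show the size of the ambiguity and should not be entered in the protocol as its mediation power. The point does not touch the .81 and .83 for the main outcomes.

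**What to change.** State which effect size and which N produced .77, and make the path and d agree. There are two ways:

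- If .12 was the input, keep the path and the power of .77, and correct the equivalent to d = .24.
- If d = .22 is the intended effect, rerun the existing Mplus simulation with a path of .11 at the N expected after attrition, and report the power it gives.

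Then reword the closing sentence on sufficiency so that it agrees with the mediation result. The cost is a wording change and at most one rerun of an existing simulation. Enrolment does not change. The downside is that the stated mediation power, or the detectable effect, may look slightly less favourable.

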## Discussion

Given the increased prevalence and disproportionate impact of heavy drinking and alcohol problems among Hispanic men in the United States, particularly Mexican-origin men, and the corresponding unmet need for alcohol-related treatment, it is essential that we address alcohol-related health disparities in this at-risk, underserved and growing population [97]. Particularly, studies suggest that racial/ethnic disparities in treatment utilization remain evident even after controlling for differences in insurance coverage, income, and education [14, 98]. Our previous work demonstrated that Hispanic patients benefit more from BMI with respect to decreased alcohol use but not alcohol related problems or treatment utilization [20, 21]. Additionally, patients who received the BMI from a Hispanic provider, and those who demonstrated lower levels of acculturation, were significantly more likely to benefit from the intervention than those who received the intervention from a non-Hispanic provider or demonstrated higher acculturation, respectively, strongly suggesting the role of cultural factors [21]. Moreover, a meta-analysis indicated that mental health interventions that account for cultural context and values are four times more effective than non-adapted interventions [91]. Taken together, these findings point toward the promise of a CA-BMI that incorporates cultural factors like familism, and acculturative stress, as in the present study. Yet, no known published study to date has compared the effectiveness of an alcohol CA-BMI in relation to a NA-BMI among non-treatment seeking, heavy drinking Mexican-origin men.

The potential for dissemination and implementation of a CA-BMI in the trauma care setting is high. The proposed comparative effectiveness trial is consistent with the call by the American College of Surgeons to provide screening and brief intervention to heavy-drinking injured patients [99]. Since 2006, the American College of Surgeons and Committee on Trauma has required that all Level I Trauma Centers have the capacity to identify injured patients with alcohol problems and provide BMI. From a behavioral health perspective, BMIs are critical components as part of the services provided in trauma care settings. Within medical settings, BMIs seem to be efficacious in part due to the window of opportunity for identifying non-treatment seeking heavy drinkers and a teachable moment for those involved in an alcohol-related injury.

A culturally adapted intervention may be more effective and better received as an alternative to currently available interventions. Patient satisfaction and provider preference will likely have significant impact on the practice of BMIs in these settings even if a CA-BMI is not superior to a NA-BMI in terms of drinking outcomes. This would be particularly true if patients and providers prefer a CA-BMI to a NA-BMI despite their equivalent efficacy or similar costs. The findings of this study will be particularly pertinent to trauma centers in states like California, Arizona, New Mexico and Texas which provide care to a largely Hispanic patient population. Moreover, given the advent of telehealth, it may also have important implications for other locations where there is a small underserved, Hispanic population. These facilities may not have the human or financial resources to provide intervention to a small yet underserved population of Hispanics. Through telehealth, CA-BMI can be provided in locales with emerging bilingual, bicultural Hispanic populations thereby increasing the public health impact of CA-BMI on the reduction of alcohol related health disparities.

Although the potential for dissemination and implementation of the findings from the proposed study are high based on the previously noted factors, it is not without potential barriers. According the World Health Organization (WHO), barriers to conducting SBI include a lack of knowledge and skills, lack of time, lack of financial benefits, lack of professional benefits, lack of diagnostic support, and the overarching organization of the health care system [100]. The proposed study will consider strategies that have been outlined previously [101–103] in order to overcome barriers and effectively implement the proposed BMI within the trauma department. Based on prior experience, our team recognizes that even highly invested trauma centers must overcome fiscal and human resource barriers to meeting the unfunded mandate of a Level I Trauma Center set by the Committee on Trauma [104]. However, we remain confident that through the engagement of key stakeholders including patients, providers and community these barriers can be overcome and CA-BMI will become an evidence-based best practice in trauma centers and emergency departments.

## Conclusion

There exists an unmet need for the treatment of heavy alcohol use, and alcohol-related problems among men of Mexican origin. This paper proposes the first comparative effectiveness study regarding the cultural adaptation of a BMI compared to a NA-BMI in the medical setting among heavy drinking men of Mexican origin. The successful adaptation and implementation of this CA-BMI may contribute to reducing the public health burden of heavy alcohol use in the United States.
